# Implementation of telemedicine for knee osteoarthritis: study protocol for a randomized controlled trial

**DOI:** 10.1186/s13063-018-2625-4

**Published:** 2018-04-17

**Keywords:** Osteoarthritis, Telemedicine, GOH, Disease management, Randomized clinical trial

## Abstract

**Background:**

Osteoarthritis (OA) is the most prevalent chronic joint disease, characterized by joint structural deterioration, pain and loss of function among the elders. It is also associated with several extra-articular symptoms (fatigue, sleep disorders, anxiety and depression) and a reduction of life quality. Studies have revealed that patients with OA benefitted from enhanced management via telemedicine. Guangdong Online Hospital (GOH) is the first officially recognized web-based hospital that provides telemedicine service in China. However, the effective implementation of GOH telemedicine (GOHT) to enhance management for patients with OA remains unknown.

**Methods/design:**

An assessor-blinded, parallel randomized controlled trial will be performed to study the feasibility and effectiveness of GOHT in the enhanced management of OA. Forty participants with knee OA will be recruited for a 6-month study. Patients meeting the inclusion criteria will be randomly allocated to receive conventional therapy (CT) or conventional therapy plus a brief GOH-based intervention (CT-GOHT). The primary outcome is the feasibility of a full-scale randomized controlled trial. The secondary outcomes include the self-reported total score of the Western Ontario and McMaster Universities Osteoarthritis Index (WOMAC), the Multidimensional Fatigue Inventory (MFI), the Pittsburgh Sleep Quality Index (PSQI) and the Hospital Anxiety and Depression Scale (HADS). Assessments will be performed at baseline, 2 weeks, 3 months and 6 months later after the initiation of the study.

**Discussion:**

This trial is intended to test the application of GOHT in the chronic management in knee OA. The hypothesis is that OA patients may receive disease management via this network platform conveniently and effectively, especially those in the remote areas of our country. GOHT telemedicine would be an attractive alternative to traditional methods for disease management in knee OA. The results could provide preliminary experiences and guidance for an upcoming full-scale randomized controlled trial (RCT) in disease management via telemedicine.

**Trial registration:**

ChiCTR: ChiCTR1800014465. Registered on 16 January 2018.

**Electronic supplementary material:**

The online version of this article (10.1186/s13063-018-2625-4) contains supplementary material, which is available to authorized users.

## Background

Osteoarthritis (OA) is a degenerative joint disease that involves the whole joint structure, including synovium, cartilage, menisci, ligaments, periarticular muscle, capsule and subchondral bone [1]. Globally, the age-adjusted prevalence of knee OA is 3.8% and of hip OA is 0.85% [2]. In China, the prevalence of symptomatic knee OA among people aged 45 years or older is 10.3% in women and 5.7% in men [3]. OA causes joint pain, functional impairment and disability [4]. Moreover, OA patients suffer from a series of extra-articular symptoms. It is reported that poor sleep is highly prevalent in OA patients and approximately 40% of OA patients have substantial fatigue which is related to pain, sleep disturbance and depressed mood [5, 6]. Besides, a considerable number of OA patients experience clinically significant depression and anxiety [7, 8]. OA has become a very serious medical problem that significantly decreases the quality of patients’ life and causes large social and economic burden [9].

As a prevalent chronic disease, OA patients are in need of long-term disease management to improve their quality of life and to prevent disability, and this demand is expected to increase greatly in the coming years with the rising incidence. As an emerging concept in health care, telemedicine, provides ways to remotely deliver consultations, treatments and monitoring disease activities [10]. Telemedicine has been shown positive results in feasibility, effectiveness and patient satisfaction in the use of chronic disease management [11, 12]. Evidence has shown that Internet-based interventions significantly improve health status and meet with high acceptance and high user satisfaction in patients with OA [13].

As an institution of Guangdong Second Provincial General Hospital, Guangdong Online Hospital (GOH) is China’s first officially recognized online hospital. Clinicians of almost all medical departments are available at this online platform (http://www.youdeyi.com/). Patients are able to receive online health services such as consultations, disease education and preliminary treatment suggestions through the telemedicine platforms with audio and video settings in the communities around the province. Our previous study has demonstrated that GOH provided a convenient platform for ankylosing spondylitis patients to receive effective disease management, especially those in the remote areas of the country [14]. The positive results encourage us to explore the role of GOHT telemedicine in the management of OA.

Therefore, we design this trial to examine the feasibility and effectiveness of GOH for knee OA management in the context of a routine clinical care. We hypothesize that GOHT can serve as a convenient telemedicine platform providing disease-enhanced management for OA patients.

## Methods/design

### Trial design

This study is a prospective, parallel randomized controlled trial (RCT) conforming to Standard Protocol Items: Recommendations for Interventional Trials (SPIRIT) guidelines (Additional file 1) [15]. The flow chart of the participants is illustrated in Fig. 1. This study will be carried out in our hospital (Fig. 2). The total duration of the study is expected to take approximately 12 months depending on the process of enrollment and follow-up visits. Both groups will be followed up for 6 months.

**Fig. 1 Fig1:**
[figure not shown]
Flow chart of trial participation

**Fig. 2 Fig2:**
[figure not shown]
The operating mode of Guangdong Online Hospital (GOH)

### Participants

#### Inclusion criteria

Participants will be qualified for inclusion when they meet the following criteria: meeting the 1986 American College of Rheumatology (ACR) classification criteria for knee OA [16]; knee OA with a pain score of at least 20 mm on a 100-mm Visual Analogue Scale (VAS) for at least 6 months [17]; Kellgren and Lawrence grades 0–3 [18]; age 50 to 75 years on the date of invitation to participate; availability of GOHT platforms in the community; ability to communicate and to understand the study.

#### Exclusion criteria

Participants will be excluded if they have any of the following conditions: OA with severe joint deformity which needs surgery; other joint diseases, including rheumatoid arthritis and joint trauma; autoimmune diseases; chronic digestive disorders including chronic gastritis and chronic hepatitis; stroke; chronic kidney diseases; cancers; dementia or substantial cognitive impairment; psychotic illness; inability to give informed consent; unable to communicate or to understand the study; and no access to a GOHT platform.

### Recruitment

First, we will set up a research team, including rheumatologists, orthopedists, clinical researchers and nurses. Staff in the team are required to learn the details of the trial well through workshops and group discussions. In order to recruit participants, an invitation letter with a brief introduction of the trial will be sent to outpatients with knee OA. Advertising posters about the trial will be placed in the local newspapers, homepage of the hospital official website and WeChat (a popular social media application in China) official account. An overview of the trial and various announcements will also be available on these platforms. In the clinic, clinicians will be responsible for identifying the potential participants from the outpatients’ reception room, and will further make an overall assessment to decide whether they meet the requirements. Participants who meet the eligibility criteria will be recruited from February 2018 to June 2018.

### Sample size

This pilot study will be conducted without performing a formal sample size calculation, as the primary outcome is the feasibility of GOHT in the enhanced management for patients with OA. We plan to recruit 20 participants for each group, allowing for a 20% dropout over the period. As the recommended sample size for a feasibility pilot trial is 12 per group [19], we anticipate that the sample size of 40 participants will provide us with sufficient information about the feasibility of the intervention including the enrollment rate and the acceptability of the intervention.

### Randomization and blinding

Recruited participants will be randomly allocated to either the CT-GOHT group (intervention) or the CT group (control) at a 1:1 ratio. Random numbers will be generated using a computer software program run by an external statistician. Each of the random numbers with the group assignment will be written on a piece of paper and packed in a sealed envelope. After baseline assessment, participants will be provided an envelope according to the randomization sequence. The outcome assessors will be blinded to the participant randomization assignment.

### Intervention group (CT-GOHT group)

In addition to conventional therapy (celecoxib, 0.2 g daily), participants in the CT-GOHT group will receive a brief repeated GOH-based management every month via the GOHT platform. The web-based management is expected to last 20–30 min for an independent intervention, containing three broad segments: encouragement, educational lectures and medical issues. The clinicians who perform the intervention have received standardized training and should be familiar with the process and the detailed contents of an intervention. To ensure standardized interventions for each participant, standard operating procedures will be provided for the researches.

Participants will be required to attend follow-up clinics at 2 weeks, 3 months and 6 months after the initiation of the trial. When the symptoms get worse, participants will be allowed to get further treatment at any time.

#### Encouragement

This session aims to comfort patients and help them to face illness with great courage. The participants will be allowed to express their negative feelings related to OA. The clinician will encourage them to be optimistic and, to make them feel that they are being cared for and listened to.

#### Educational lectures

In this session, the participants will receive background knowledge of OA, including pathogenesis, risk factors, clinical manifestations, pharmacological therapies and prognosis of OA. Besides, some feasible non-pharmacological therapies, like dietary control, weight loss and proper exercise, will be recommended to the participants based on their personal conditions. The importance of long-term disease management in the rehabilitation of OA will also be emphasized. If there are any questions related to knee OA or the study, the participants are expected to receive responses from the clinician via GOH.

#### Medications

The clinician will emphasize the importance of medications in disease remission and remind participants to take medications on time at each GOHT visit. Besides, the clinician will tell participants the potential side effects medications may cause. If possible severe adverse reactions emerge, the participants should withdraw from the trial and get further treatments.

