### Control group

Participants in the CT group will receive conventional therapies (celecoxib, 0.2 g daily). They will not receive any network-enhanced management via GOH. Similarly, participants will be required to attend follow-up clinics at 2 weeks, 3 months, 6 months after the initiation of therapy. Participants will be allowed to receive further treatments when their symptoms get worse. Any additional treatments received during the follow-up period will be recorded.

Participants in both groups are free to withdraw from the study at any time, but the withdrawal rates and reasons will be recorded.

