### Outcome assessments

The outcome assessments will be made at baseline, 2 weeks and 3 month later after the initiation of the study and at the end of 6 months. All measurements of participants will be performed by a researcher blinded to the group allocation.

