#### Primary outcome measures

The primary outcome measurement is feasibility of the study. It will be evaluated by recording the proportion of patients with knee OA who meet eligibility criteria but decline to participate; the adherence to the intervention and the withdrawal rates. Besides, we will investigate the satisfaction in using GOHT among participants in the CT-GOHT group (Fig. 3).

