### Withdrawal

Participants are free to withdraw from the study at any time, which will be informed during the consent process. If a participant chooses to withdraw, they will be asked to provide reasons and the reasons for withdrawal will be recorded. Besides, participants can discontinue the study at any time point if they experience any adverse events. The adverse events will be recorded.

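### A possible severe adverse reaction is made a reason to leave the trial rather than to stop celecoxib, so later outcome scores are lost needlessly

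*Protocol article*

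**What the plan says.** The rule is in the Medications section, within the description of the intervention group: "If possible severe adverse reactions emerge, the participants should withdraw from the trial and get further treatments".

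The surrounding provisions are these:

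- **Treatment.** For the intervention arm: "In addition to conventional therapy (celecoxib, 0.2 g daily), participants in the CT-GOHT group will receive a brief repeated GOH-based management every month". The Control group section gives the same celecoxib dose without the telemedicine programme.
- **Worsening symptoms.** The intervention section states: "When the symptoms get worse, participants will be allowed to get further treatment at any time". The Control group section has an equivalent permission and adds: "Any additional treatments received during the follow-up period will be recorded".
- **Assessments.** From Outcome assessments: "The outcome assessments will be made at baseline, 2 weeks and 3 month later after the initiation of the study", with a last assessment at 6 months.
- **Leaving the study.** The Withdrawal section says "participants can discontinue the study at any time point if they experience any adverse events". Reasons for withdrawal and adverse events are to be recorded. No assessment after withdrawal is described.
- **Primary outcome.** Feasibility includes "the adherence to the intervention and the withdrawal rates".
- **Analysis.** WOMAC, MFI, HADS and PSQI go into a repeated-measures mixed-effect model (Planned statistical analysis). The Discussion expects the preliminary effect data to inform power calculations for a larger trial.

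**The concern.** The instruction is directive, it is triggered by a reaction that is only possible, and what it ends is trial participation rather than the drug. Three features make this a poor rule for this design.

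First, celecoxib is common to both arms. The question is what the telemedicine programme adds, and someone who has had to stop celecoxib is still informative about that.

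Second, leaving the trial is not needed to obtain care. Participants whose symptoms worsen may have further treatment, and nothing says they must leave in order to have it.

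Third, nothing in the article restores follow-up after an exit.

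At stake are the later secondary scores of people who could have kept attending visits already in the schedule. The mixed model uses the scores collected before exit but cannot recover those never taken. The missing scores would also not be a random subset, because they are lost as a result of a severe reaction. Directed exits also enter the withdrawal rate, where they say little about willingness to stay. That count is nevertheless accurate, and the recorded reasons allow such exits to be identified, so the lasting loss is the scores.

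**Working it through.** The plan states no figure for this point, so there is none to reproduce. The size follows from the visit schedule and sample size.

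**Inputs from the protocol article**

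- 20 participants per arm, 40 in total, with a 20% dropout allowance (Sample size).
- 3 post-baseline assessments: 2 weeks, 3 months, 6 months (Outcome assessments).
- 4 instruments: WOMAC, MFI, HADS, PSQI (Secondary outcome measures).

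**Planned post-baseline scores per arm**, counting one score per instrument per visit:

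20 × 3 × 4 = 240.

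**Loss per directed exit**

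| Time of exit | Visits lost | Scores lost | Share of arm's 240 |
|---|---|---|---|
| Before 2 weeks | 3 | 3 × 4 = 12 | 12/240 = 5.0% |
| 2 weeks to 3 months | 2 | 2 × 4 = 8 | 8/240 = 3.3% |
| 3 to 6 months | 1 | 1 × 4 = 4 | 4/240 = 1.7% |

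The percentages do not depend on the number of instruments: 3 of the arm's 60 planned post-baseline visits is also 5.0%. Whatever the timing, each exit before the last visit removes one of 20 participants (5%) from that arm's 6-month data.

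**Effect on the withdrawal rate per exit**

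- One arm: 1/20 = 5 percentage points.
- Both arms pooled: 1/40 = 2.5 percentage points.

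**Dropout allowance**

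0.20 × 20 = 4 per arm, leaving 16. The allowance may already cover these exits.

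**How often the rule might operate**

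The article gives no rate of severe reactions, so the rates below are assumptions, with the rule applied in both arms. Expected exits are 40p and the chance of no exit is (1 − p)^40.

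| Assumed p | Expected exits among 40 | Chance of none |
|---|---|---|
| 1% | 0.4 | 0.99^40 = 0.669 (67%) |
| 5% | 2.0 | 0.95^40 = 0.129 (13%) |
| 10% | 4.0 | 0.90^40 = 0.015 (1%) |

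**The case against.** The strongest reply is that the harm rests partly on silence. The Medications section never says that scheduled assessments stop, and a full protocol might provide for follow-up after withdrawal. Silence in a condensed article would indeed be no finding. Here, however, the article states an instruction, and what it tells participants to leave is the trial. An analysis plan cannot supply assessments that were never made. If only stopping treatment was meant, the sentence needs correcting anyway.

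A second reply is that the sentence belongs to an account of what the clinician covers at a telemedicine visit, while the Withdrawal section is permissive. That is fair as to context. It also means that the text does not settle whether the rule applies to the control arm, and for that reason no difference between arms is claimed.

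Third, worsening osteoarthritis symptoms and a severe drug reaction are different clinical events, and the recording of additional treatments is stated only for the control group. Both points are correct, so this is not a contradiction within the plan. The comparison shows only that the plan elsewhere lets participants take further treatment without requiring them to leave.

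Fourth, celecoxib is the only named conventional therapy and medication reminders are part of the intervention, so a participant who stops the drug no longer receives either regimen as described. That is a matter for interpretation and reporting; it is not a reason to stop measuring outcomes.

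Finally, little is at stake. This is a 40-person pilot with feasibility as its primary outcome. Its dropout allowance leaves 16 per arm against the 12 it cites, and even the 10% assumption gives about 2 exits per arm against an allowance of 4. This stands, and it keeps the point minor.

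**Conclusion.** The concern holds, as a minor one. The rule is badly fixed: it discards obtainable outcome data and gives no protection that stopping celecoxib and treating the reaction would not give. Each exit costs between 1.7% and 5.0% of one arm's planned post-baseline scores. The total cannot be known from the article; at the 1% rate the rule would more likely than not never be used.

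The conclusion rests on reading the instruction literally, on there being no described assessment after withdrawal, and, for the expected numbers, on assumed reaction rates applied in both arms. The withdrawal count itself is not wrong, and the planned sample size need not change.

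**What to change.** In the Withdrawal section, state for both arms that:

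1. a severe reaction leads to stopping celecoxib and appropriate treatment, with the clinical criterion set by the clinical team;
2. scheduled assessments continue to 6 months unless the participant withdraws consent;
3. discontinuation of treatment is reported separately from withdrawal from the study.

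Reword the Medications section to match, for example: stop celecoxib, obtain further treatment, and continue the scheduled assessments.

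The cost is a short change in two places and one extra field on the case report form, since the visits are already scheduled and withdrawal reasons already recorded. The drawback is that some later scores will come from participants no longer taking celecoxib, which the report should state.

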### Control group

Participants in the CT group will receive conventional therapies (celecoxib, 0.2 g daily). They will not receive any network-enhanced management via GOH. Similarly, participants will be required to attend follow-up clinics at 2 weeks, 3 months, 6 months after the initiation of therapy. Participants will be allowed to receive further treatments when their symptoms get worse. Any additional treatments received during the follow-up period will be recorded.

Participants in both groups are free to withdraw from the study at any time, but the withdrawal rates and reasons will be recorded.

### Outcome assessments

The outcome assessments will be made at baseline, 2 weeks and 3 month later after the initiation of the study and at the end of 6 months. All measurements of participants will be performed by a researcher blinded to the group allocation.

#### Primary outcome measures

The primary outcome measurement is feasibility of the study. It will be evaluated by recording the proportion of patients with knee OA who meet eligibility criteria but decline to participate; the adherence to the intervention and the withdrawal rates. Besides, we will investigate the satisfaction in using GOHT among participants in the CT-GOHT group (Fig. 3).

#### Secondary outcome measures

The Western Ontario and McMaster Universities Osteoarthritis Index (WOMAC) [20] will be used to measure pain, stiffness and physical function in the knee. WOMAC, a self-administered health-status instrument for patients with knee OA, consists of 24 items within three subscales: pain (five items), stiffness (two items) and physical function (17 items). We will be use the VAS to measure the items of pain. The WOMAC scores will be standardized to a 0 (worst) to 100 (best) total score range.

The Multidimensional Fatigue Inventory (MFI) [21] will be used to evaluate fatigue. The MFI, widely used for measuring fatigue, is a 20-item self-report instrument. It covers the following dimensions: general fatigue, physical fatigue, reduced activity, reduced motivation and mental fatigue.

The Hospital Anxiety and Depression Scale (HADS) [22] will be used to assess anxiety and depression. The HADS is a widely used instrument to measure mental condition in many chronic diseases. It is a 14-item scale with seven items for anxiety (HADS-A) and seven for depression (HADS-D). Scores ranged from 0 to 21 for each subscale.

The Pittsburgh Sleep Quality Index (PSQI) [23] will be used to assess sleep quality. The PSQI, Global PSQI with a total score ranging from 0 to 21, is a standardized self-administered questionnaire for the assessment of sleep quality over the previous 1 month. It contains several sections to assess subjective sleep quality, sleep latency, sleep duration, sleep efficiency, sleep disturbances, use of sleeping medications and daytime dysfunctions.

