### Planned statistical analysis

To evaluate the feasibility of the study, we will calculate the proportion of enrolled participants out of all eligible patients, participants who adhered to the intervention and the dropout rates. Besides, a patient satisfaction survey for the use of GOHT will be collected and analyzed.

Means and standard deviations will be used to describe between-group statistics of WOMAC, MFI, HADS and PSQI. All these variables will be analyzed using a repeated-measures mixed-effect model with terms for age, sex, Body Mass Index and treatments. The measurement data will be assessed for normal distribution using Shapiro-Wilk’s test for both groups. Independent samples’ *t* test will be used for the comparison of two-independent samples. Non-parametric tests (Mann-Whitney *U* test) will be used in cases of abnormal distribution. Statistical analysis will be processed by SPSS software (version 19.0). The categorical variables will be compared by a chi-square test. *P* < 0.05 will be accepted as the threshold for statistical significance.

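### The 2-week PSQI looks back 1 month, so about half of its window precedes treatment; the PSQI effect should be estimated from 3 and 6 months only

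*Protocol article*

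**What the plan says.** All places are in the protocol article.

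- **Recall period.** Under Secondary outcome measures, the PSQI "is a standardized self-administered questionnaire for the assessment of sleep quality over the previous 1 month". No shortened recall version is mentioned.
- **Visits.** Under Outcome assessments: "The outcome assessments will be made at baseline, 2 weeks and 3 month later", with a last assessment at 6 months. The Methods/design part of the Abstract lists the secondary scales, PSQI among them, and continues: "Assessments will be performed at baseline, 2 weeks, 3 months and 6 months later after the initiation of the study". Neither place makes an exception for PSQI.
- **Order of events.** Under Randomization and blinding: "After baseline assessment, participants will be provided an envelope according to the randomization sequence". Baseline PSQI is thus scored before allocation.
- **Time origin.** Under Control group, "participants will be required to attend follow-up clinics at 2 weeks, 3 months, 6 months after the initiation of therapy". Elsewhere the origin is worded as the start of the study or of the trial.
- **Randomised component.** Under Intervention group, "participants in the CT-GOHT group will receive a brief repeated GOH-based management every month via the GOHT platform". The day of the first session is not given. Celecoxib is given in both arms.
- **Analysis.** Under Planned statistical analysis, after WOMAC, MFI, HADS and PSQI are named: "All these variables will be analyzed using a repeated-measures mixed-effect model with terms for age, sex, Body Mass Index and treatments". The 2-week PSQI is not set aside.

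**The concern.** An instrument with a 1-month recall, completed 14 days after treatment starts, mixes sleep before and after that start. The pre-treatment days belong to the period already scored at baseline. By randomisation they carry no expected difference between arms, so they dilute the 2-week contrast. Adjusting for baseline PSQI would improve precision but would not undo this dilution.

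Two things are at stake. A null 2-week sleep result could be misread as absence of early benefit. In addition, the Discussion says the preliminary effect data are meant to inform power calculations for a larger trial, and any PSQI effect that draws on the 2-week value would enter those calculations too small. The error runs toward no difference, so it does not create a false positive.

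**Working it through.** The article states no PSQI effect size, SD or power, so there is no figure of its own to reproduce. The check is on the recall window.

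**Inputs.** Recall of 1 month, read as M = 28, 30 or 31 days (Secondary outcome measures). First follow-up on day 14 (Outcome assessments). Day 0 is taken as the start of therapy, as worded under Control group, with baseline scored at or just before it.

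**Share of the 2-week window before treatment** = 1 − 14/M:

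- M = 28: 1 − 14/28 = 50.0%
- M = 30: 1 − 14/30 = 53.3%
- M = 31: 1 − 14/31 = 54.8%

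The share on treatment is 50.0%, 46.7% and 45.2%.

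**Later visits.** At 3 months (about day 90) a 31-day window opens on day 90 − 31 = 59; at 6 months (about day 180) it opens on day 180 − 31 = 149. The pre-treatment share is 0% at both.

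**Illustrative effect on a pooled estimate.** Three assumptions are needed, none of them in the article: respondents weight all recalled days equally; the true effect is complete from day 0 and constant; the model averages the three follow-ups with equal weight. With M = 30 the recovered fraction is

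(0.467 + 1 + 1)/3 = 0.822, an attenuation of about 18%.

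With M = 28 it is (0.500 + 2)/3 = 0.833, and with M = 31 it is (0.452 + 2)/3 = 0.817.

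**Sensitivity to the true effect at 2 weeks** (M = 30):

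- Half the full effect, present since day 0: true average (0.5 + 1 + 1)/3 = 0.833; observed (0.5 × 0.467 + 1 + 1)/3 = 0.744; ratio 0.893, so about 11% attenuation.
- No effect yet: (0 + 1 + 1)/3 = 0.667 with or without the recall mismatch, so the mismatch adds nothing.

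**Consequence for a future sample size.** At the same SD, the required number scales with 1/effect². A fraction of 0.822 gives 1/0.822² ≈ 1.5 times the number needed, under the same three assumptions.

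**The case against.** The strongest reply is that the mismatch is real but its consequence is inferred.

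- **Pooling is not stated.** A reader might infer that the 2-week visit counts as much as 3 and 6 months in one averaged treatment effect. The article names the model's terms but not the contrast, and it also mentions two-sample tests that could be applied visit by visit. Such detail may sit in an analysis plan that is not shown. This stands: the 18% is conditional. A visit-specific analysis would leave the 3- and 6-month results untouched, though the 2-week contrast would still be diluted.
- **A larger loss is tempting.** If baseline is modelled as a response, (0 + 0.467 + 1 + 1)/4 = 0.617 looks like a 38% loss. The article does not say baseline is a response. Even if it were, that model already gives (0 + 1 + 1 + 1)/4 = 0.75 with no recall problem, a 25% loss shared by every scale. The recall part is 0.617/0.75 = 0.822, again 18%.
- **About 47% is not a ceiling.** It rests on equal weighting of recalled days. If recent nights weigh more, more of the effect shows at 2 weeks. Nor is the 18% a strict bound in the other direction: a first session on day 7 with an instant full effect would leave 7/30 = 23% of the window, and (0.233 + 2)/3 = 0.744.
- **Early timing is a separate matter.** With monthly sessions, about one at most precedes week 2. Little effect by then would touch all four scales and is not a PSQI recall problem; it makes the recall loss smaller.
- **Fig. 5 is not shown.** It holds the assessment schedule and could limit PSQI by visit. Nothing in the text suggests that it does, but the point depends on it.
- **The setting is modest.** This is a 40-person pilot with feasibility as primary outcome and no formal sample size calculation. One of three follow-ups of one secondary scale is affected.

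These objections reduce the size and severity. They do not remove the overlap between a 1-month recall and a 2-week visit.

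**Conclusion.** The point holds as a minor one. On the article's own text, about half of the 2-week PSQI window (50% to 55%, depending on the length of a month) precedes treatment and overlaps the baseline window, so the 2-week PSQI contrast is biased toward no difference. This needs only that day 0 is close to the start of treatment and that the usual 1-month form is used at 2 weeks.

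The 18% attenuation of a pooled PSQI effect is an illustrative high case for an effect present since day 0. It needs equal recall weighting, an immediate constant effect and equal averaging of the follow-ups. It falls to about 11% if half the effect is present at 2 weeks, and to nothing if none is. The documents do not support reading this as a flaw in the trial's sleep results as a whole: PSQI at 3 and 6 months is unaffected, and so are the feasibility outcomes. The conclusion is conditional on Fig. 5 not already restricting PSQI by visit.

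**What to change.** State that the PSQI treatment effect is estimated from the 3- and 6-month assessments only, with baseline PSQI taken into account. For the 2-week visit, either do not collect PSQI, or collect it and report it descriptively outside the treatment-effect model, noting that its recall period reaches back before treatment. Check Fig. 5 and make it agree with the text.

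This takes one line in the assessment schedule and one in the analysis section. Dropping the form also spares participants a questionnaire. The price is the loss of an early sleep reading, or of its use in the model, for one secondary scale; that reading cannot separate sleep before treatment from sleep on treatment.
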